#### Advice to stay active

Experimental and control participants will receive the same advice to stay active protocol. In the first session, all participants will receive a blank booklet of activities developed by the researchers, in order to register their activities of daily living performed during the week (e.g., eating, cooking, bathing, brushing teeth, shaving, changing clothes, housework, financial management, proper medication, time away from home, and social interaction activities). This booklet of activities should be presented to the physiotherapist in the next session. Also, both experimental and control group will receive the session at Augusto Motta University Centre (UNISUAM) outpatient physiotherapy. Participants will be submitted to the same protocol and there will be no modification of the protocol during the study.

The intervention will be performed by a physiotherapist ([name]) with 3 years of clinical experience. All participants will receive five sessions of advice to stay active in their daily living activities, information on physical activity, imaging tests, and sciatica. These sessions will be performed in person and individually, lasting 25–30 minutes [36], and there will be a gap of two week between the sessions. Advice to stay active will focus on two themes: potential harmful effects of pain and beneficial effects of stay active on pain [18]. In the harmful effects of pain, we will discuss avoidance of daily-life activities [18, 37, 38], prolonged rest [18], sedentary lifestyle and imaging [11, 39]. In the beneficial effects of stay active on pain, we will discuss the benefits of staying active [17, 39–43], how to avoid bed rest and the positives aspects of returning to work as soon as possible [39, 40, 44], practising physical activity [39, 40, 45], understanding sciatica, pain tolerance and favourable prognosis [17, 40]. In the first four sessions of advice to stay active, one discussion point of harmful effects and one discussion point of beneficial effects will be addressed in each session. Participants will receive a summary of the content covered in all previous sessions at the last session.

#### Neural management

Neural management will be delivered individually by a physiotherapist ([name]) with 9 years of clinical experience. Participants will receive neural mobilisation techniques and soft tissue mobilisation techniques for 30 minutes per session, 10 weekly sessions, considering the participant’s availability. All participants in neural management will be treated by the same physiotherapist, and the techniques will be performed at the symptomatic limb. The treatment sessions will be conducted at UNISUAM outpatient physiotherapy.

In each neural management session, participants will receive the following protocol in the affected lower limb, based on a previous study [28]:

Myofascial release techniques in the piriformis and biceps femoral muscles in the prone position, performed manually by the therapist using the thumb to sliding in the transverse direction of the piriformis muscle for 15 repetitions, and a longitudinal direction of the biceps femoris muscle for 5 repetitions. When locating any tissue barrier (myofascial trigger point), sustained pressure in the region will be applied for 90 seconds.Soft tissue techniques including cross-fibre friction technique used to reduce the entrapment of the sciatic nerve along the nerve pathway. Therefore, a friction technique will be applied in the craniocaudal direction on the sacroiliac joint bilaterally for 15 repetitions with the patient in the prone position. The friction technique will be applied with manual contact directly on the ligaments of the sacroiliac joint.Hip joint mobilisation techniques will be performed in supine position for 1-minute each technique. The therapist will be at the contralateral side of the affected limb, and the patient will be positioned with a hip flexion around 90 degrees and maximum knee flexion. The asymptomatic limb will be extended. The anteroposterior technique will be performed by mobilising the hip joint with the therapist’s hand located in the knee and performing the posterior glide in the hip joint. The therapist will also perform an internal rotation hip mobilisation, positioned at the same side of the affected limb, and with both hands located in the middle area of the femur.Neural mobilisation will be performed after the initial techniques to improve the excursion of the sciatic nerve. Sliding techniques will be performed as neural mobilisation manoeuvres of the sciatic nerve with hip flexion and extension associated with ankle plantar flexion and dorsiflexion. The therapist will perform 3 sets of 30 oscillations for 1 minute, with the patient in supine position and knees extended. Patient will rest for 1 minute among the sets. The range of motion should not cause pain or paraesthesia symptoms, and the range will gradually increase according to the patient’s response to the application of the technique.

### Criteria for discontinuing or modifying allocated interventions

The allocated intervention could be modified or discontinued once a participant requests explicitly or refuse to continue the treatment or follow-up assessment, and the reason will be fully reported. The study will be discontinued in case of serious adverse events (any significant disability, hospitalisation, life-threatening, and death) occur that make continuing the study harmful for the participants regardless if related to the intervention (or control) or not. Ancillary and post-trial care (e.g., provision and/or cover for additional health care of immediate adverse events related to trial procedures) will be provided for participants who suffer sustained harm as a result of their involvement in this trial at no costs.

### Outcomes measures

The primary outcomes will be leg pain intensity and functional limitation. Secondary outcomes will include neuropathic symptoms, sciatic neurodynamic, pain modulation, and psychosocial factors (detailed in S2 File). The follow-ups will be performed in 5 weeks, 10 weeks, and 26 weeks after randomisation. The follow-up assessment at 10 weeks after randomisation will be considered the primary time-point. In addition, adverse events and patient satisfaction will also be assessed.

#### Primary outcome

*Pain intensity*. Pain intensity will be measured using the Numeric Pain Rating Scale (NPRS) from 0 (no pain) to 10 (worst pain possible). Participants will be asked to rate their leg pain and low back pain intensity at the evaluation moment. The NPRS is a common scale in pain studies, including those with sciatica and has good reproducibility levels [46]. The minimally clinically important difference considered in the current study will be an effect size of 0.2. The duration of pain will be recorded in months.

*Functional limitation*. Functional limitation will be investigated using the Patient-Specific Functional Scale (PSFS). The PSFS is a self-reported measure widely used to assess limited functional activities in patients with musculoskeletal disorders, presenting excellent reliability [47]. Participants will be asked to identify up to three important activities they are unable to perform or are restricted as a result of their pain. Each activity will be classified on an 11-point Likert scale regarding the current level of difficulty, which 0 means “unable to perform activity” and 10 “able to perform activity at the level as before injury”, and the mean of the three activities will be calculated. PSFS has ease applicability and can be used clinically as an outcome measure [48, 49].

#### Secondary outcomes

*Neurological assessment*. The neuropathic symptoms will be assessed by a clinical examination for neurological assessment and the painDETECT questionnaire. The clinical examination for neurological assessment will include muscular function and sensory abnormalities evaluation [50–53].

*Sciatic neurodynamic*. The sciatic neurodynamic will be assessed by the range of motion of the hip during the straight leg raise test, the cross-sectional area of ​​the sciatic nerve, and the echogenicity ratio [54–62].

*Conditioned pain modulation*. Cold pressor test (CPT) will assess the conditioned pain modulation (CPM). The CPT is a psychophysical test used to assess the CPM, where the cold water (between 1°C and 4°C) is the pain conditioning stimulus, and pressure pain threshold (PPT) is the test stimulus. The CPT is an appropriate method to assess the descending nociceptive inhibitory system [63, 64].

*Psychosocial factors*. Brief Psychological Screening Questions (BPSQ) will be included to assess the psychosocial factors. The BPSQ is a self-reported questionnaire that assesses the influence of psychosocial factors on an individual’s health. Anxiety symptoms, social isolation, catastrophisation, depression symptoms, kinesiophobia and perceived stress are the domains assessed [65, 66]. In addition, self-efficacy will be evaluated by the isolated item “I am confident I can cope with my condition” [67].

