### Adherence to interventions, adverse events, and assessment of patient satisfaction

Adherence to home treatment will be assessed through the activity’s agenda, in which participants must register the activities that were performed at home in the days between the sessions, in order to remain active. High adherence will be defined as ≥ 70% attendance at sessions [68].

Serious adverse events and adverse events that occurred during the intervention will be assessed by a self-reported questionnaire developed by the researchers to register the symptom and/or adverse event, with duration and intensity details. Serious adverse events will include any significant disability, hospitalisation, life-threatening, and death, and will be reported immediately to the researchers and ethics committee.

Patient satisfaction assessment will be performed through MedRisk, a questionnaire capable of measuring the level of satisfaction of the patient who will be receiving interventions through physiotherapists. MedRisk consists of 20 items, 10 items related to the therapist-patient interaction, 2 items that are considered global and 8 items that evaluate other domains. Participants will score patient satisfaction using a Likert scale ranging from 1 (strongly disagree) to 5 (strongly agree). The higher the score, the higher the satisfaction [69].

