#### Secondary analysis

The between-group differences for the secondary outcome considering the change in neuropathic symptoms, sciatic neurodynamic, conditioned pain modulation, and psychosocial factors from baseline to each 5, 10- and 26-weeks after randomisation will be calculated using mixed linear models using the interaction terms of treatment group versus time.

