#### Tertiary analysis

The patients’ adherence, serious adverse events or adverse events, and patient satisfaction will be described and presented as mean and standard deviation for continuous variables and as absolute values and percentage for categorical variables.

We will also carry out the mediation analysis to understand whether sociodemographic factor, pain characteristics, and psychosocial factors affect the primary outcomes. The mediator’s analysis will be performed by simple mediation analysis, considering one variable per model, and we will use data collected at baseline. Models will be designed separately for pain intensity and functional limitation, considering the treatment group as independent variable (X), pain intensity and functional limitation as dependent variable (Y), and sociodemographic factor, pain characteristics, and psychosocial factors as mediators (M).

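### Adverse events are captured only by participant self-report during the intervention, and no stated route takes motor or sensory worsening found by the blinded examiner into the harms results

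*Protocol article*

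**What the plan says.** Under Secondary outcomes, the examination belongs to the neuropathic-symptoms outcome: "The neuropathic symptoms will be assessed by a clinical examination for neurological assessment and the painDETECT questionnaire". Its content is motor and sensory: "The clinical examination for neurological assessment will include muscular function and sensory abnormalities evaluation". Outcomes measures gives the visits, "The follow-ups will be performed in 5 weeks, 10 weeks, and 26 weeks after randomisation", and refers the reader to a supplement for the detail of the secondary outcomes (S2 File).

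The Secondary analysis section states one use of these data. It covers "The between-group differences for the secondary outcome considering the change in neuropathic symptoms" and the other secondary outcomes, with change "from baseline to each 5, 10- and 26-weeks after randomisation will be calculated using mixed linear models" and a treatment-by-time interaction.

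Harms are handled separately. The section on adherence, adverse events and satisfaction says: "Serious adverse events and adverse events that occurred during the intervention will be assessed by a self-reported questionnaire". The form records the symptom or event with its duration and intensity. Significant disability counts as a serious adverse event and is reported at once to the researchers and the ethics committee. The Tertiary analysis section adds that "serious adverse events or adverse events, and patient satisfaction will be described and presented" with means, counts and percentages.

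The section on randomisation and blinding says that the assessing physiotherapist is blinded to allocation and that participants are not.

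**The concern.** The experimental treatment acts on the sciatic nerve and its surrounding tissue, and a neurologic deficit is one of the five diagnostic findings at entry. The trial examines motor and sensory function by a blinded assessor, on the same schedule in both arms. That is a sound basis for comparing neurological deterioration between arms, but the stated analysis reduces it to a group-level change.

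The stated harms source is weaker for this purpose in three ways:

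- It comes from participants who know their treatment.
- It depends on the participant noticing and reporting the change.
- It covers events during the intervention, whereas the examination continues to 26 weeks.

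Contact also differs between arms: ten treatment sessions plus five advice sessions against five advice sessions alone. This may make self-report less comparable between them.

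At stake is the completeness of the safety results. The trial could report few or no neurological adverse events while its own examination records show individual patients who worsened. Unblinding for a serious adverse event, and any decision to discontinue the study, also depend on events being recognised.

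**Working it through.** **The two data streams side by side**

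| | Neurological examination | Adverse events |
|---|---|---|
| Source | Blinded assessor | Participant questionnaire, unblinded |
| Timing | Baseline, 5, 10 and 26 weeks | During the intervention |
| Stated analysis | Group difference in change, mixed linear model | Counts and percentages |
| Stated link to the other stream | None | None |

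The text shown leaves two kinds of worsening out of the harms results:

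1. Worsening found on examination that the participant does not report.
2. Worsening that first appears after treatment. Neural management is 10 weekly sessions, so the last visit falls about 26 − 10 = 16 weeks after it ends.

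**The plan's own figure**

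The only computed design figure is the sample size of 210, or 105 per group. Inputs from the sample size section are f = 0.2, 2 groups, 3 evaluations, alpha 0.05, power 90% and 15% loss. The article gives no correlation between repeated measures, so 0.5 is assumed. For the between-factors test in repeated-measures ANOVA, with noncentrality λ = f²·N·m / [1 + (m − 1)ρ], the smallest even N is 178 (power 0.9015). Then 178 / 0.85 = 209.4, rounded up to 210. The figure reproduces under that assumption, and this point does not depend on it. It does give the expected number remaining per arm: 178 / 2 = 89, which agrees with 105 × 0.85 = 89.25.

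**Why a mean change does not replace a count**

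The article states no scale for the examination, so take an assumed score of +1 (improved), 0 (unchanged) or −1 (worsened):

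- Arm A: 40% improve and 5% worsen. Mean = 0.40 − 0.05 = +0.35.
- Arm B: 35% improve and none worsen. Mean = +0.35.

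The means are equal, yet arm A has 105 × 0.05 = 5.25, about 5, worsened patients. Across assumed worsening rates of 2% to 10%, the number is 2.1 to 10.5 of 105.

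**What a count could show at this size**

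With zero events in n patients, the exact one-sided 95% upper bound is 1 − 0.05^(1/n). The chance of seeing at least one event at true rate p is 1 − (1 − p)^n.

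| n per arm | Upper bound if 0 events | p = 1% | p = 2% | p = 5% |
|---|---|---|---|---|
| 105 | 2.8% | 0.65 | 0.88 | 0.995 |
| 89 | 3.3% | 0.59 | 0.83 | 0.990 |

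The row for 89 is the realistic one, because it allows for the plan's own 15% loss. The rates are assumptions; the article gives none.

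**The case against.** The strongest reply is that this is a condensed article. Outcomes measures says "Secondary outcomes will include neuropathic symptoms, sciatic neurodynamic, pain modulation, and psychosocial factors (detailed in S2 File"), and that file, the schedule figure and any full protocol were not available for this review. Scoring rules or a per-patient shift table could be there, and the sections quoted do not contradict one another. This stands as a caution: the point concerns what the article states, and it cannot be said that no such table exists. It does not remove the point, because the article itself fixes the source and the window of adverse-event capture. Followed as written, that rule omits worsening which the trial records.

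A reader might infer that a patient whose deficit worsens would never be counted as a harm. The documents do not support this. New numbness or weakness noticed during treatment can be entered on the questionnaire, and significant disability meets the definition of a serious adverse event.

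A reader might also infer that neurological loss is the most relevant harm of the technique, or the only one measured objectively. The text supports neither. The instruction to keep movement within a range free of pain and paraesthesia is a safeguard against provoking symptoms; it does not show that lasting deficit is expected. Motor and sensory testing depend partly on patient response and examiner judgement, and the trial has other assessor-measured outcomes, such as straight leg raise and ultrasound.

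Finally, a count of worsened patients will include measurement error and the natural course of sciatica, and attribution to treatment is weaker at 26 weeks. This is correct. It affects both arms, so it is a reason to define worsening in advance and to read the count as a comparison between arms.

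**Conclusion.** The point holds in a limited form. On the article's text, examiner-found worsening has no stated route into the harms results, and its only stated analysis is a group-level change. The loss is confined to worsening that the participant does not report or that first appears after treatment.

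Its size cannot be derived from the article, which gives neither a worsening rate nor an examination scale. Under assumed rates of 2% to 10% it concerns at most about 2 to 10 of 105 patients per arm, since some of them would report the change themselves. No figure in the plan is wrong, and the primary analysis and sample size are untouched. The conclusion assumes that S2 File and any full protocol do not already supply the link. It is a cheap improvement to the safety reporting.

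**What to change.** Add to the Tertiary analysis, for each arm at 5, 10 and 26 weeks, the number and percentage of participants with a new or worsened motor or sensory finding against their own baseline. Give the between-arm difference with a confidence interval. Define worsening in advance on the examination scale in use, because some participants will have a deficit at entry. Give the number examined at each visit as the denominator.

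In the adverse-events section, state that worsening found by the examiner is passed on, without knowledge of allocation, for adverse-event recording, and that this includes findings at the 26-week visit. How such a participant is then managed is for the investigators to decide. If S2 File or the full protocol already contains such a rule, a cross-reference is enough.

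The cost is one table from data already collected, one definition and one sentence on notification. It needs no extra visits, procedures or participants. The counts will carry some noise in both arms, and the text accompanying the table should say so.

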### Adherence to interventions, adverse events, and assessment of patient satisfaction

Adherence to home treatment will be assessed through the activity’s agenda, in which participants must register the activities that were performed at home in the days between the sessions, in order to remain active. High adherence will be defined as ≥ 70% attendance at sessions [68].

Serious adverse events and adverse events that occurred during the intervention will be assessed by a self-reported questionnaire developed by the researchers to register the symptom and/or adverse event, with duration and intensity details. Serious adverse events will include any significant disability, hospitalisation, life-threatening, and death, and will be reported immediately to the researchers and ethics committee.

Patient satisfaction assessment will be performed through MedRisk, a questionnaire capable of measuring the level of satisfaction of the patient who will be receiving interventions through physiotherapists. MedRisk consists of 20 items, 10 items related to the therapist-patient interaction, 2 items that are considered global and 8 items that evaluate other domains. Participants will score patient satisfaction using a Likert scale ranging from 1 (strongly disagree) to 5 (strongly agree). The higher the score, the higher the satisfaction [69].

### Data collection and management

Patient’s characteristics at baseline assessment will be collected immediately before randomisation. All the data collected, and outcomes will be obtained using printed questionnaires. The original data will be scanned as image files by a research assistant and shared with a second research assistant. Data integrity will be audited by regularly scrutinising data for omissions and errors by double entered with automated checks in Microsoft Excel spreadsheet (Microsoft Corporation) performed by [name] remotely. Discrepancies will be explored and resolved by checking the original data.

Participants will be identified by an individual trial number to ensure confidentiality, and confidentiality regarding the data collected in all stages will be guaranteed by stored on password-protected servers. The paper-form data will be stored in locked filing cabinets at the Postgraduate Program in Rehabilitation Sciences. Data will only be accessible to the research team. All statistical analyses will be performed using the individual number of each participant and the statistician will be blinded to the group. The results will be presented by group data and any individual data will be spread to ensure confidentiality is preserved.

#### Baseline assessment

Participants will be referred for baseline assessment consisting of the demographic (age, sex, weight, height, house income, marital state, profession, and education level), clinical (comorbidities, duration of pain, location of pain on the body map, average pain intensity, pain area, and medication), and lifestyle (physical activity and quality of sleep).

Physical activity will be evaluated using the short International Physical Activity Questionnaire (IPAQ) and categorised as low (<600 MET x min/week or <150 minutes per week of moderate intensity physical activity), moderate (600–3000 MET x min/week or 150–750 minutes per week of moderate intensity physical activity), or high (> 3000 MET x min/week or > 750 minutes per week of moderate intensity physical activity) [70, 71].

Sleep quality will be evaluated using the question of sleep quality assessment of the Pittsburgh Sleep Quality Index (PSQI) [72]. Each participant will answer, “During the past week, how would you rate your sleep quality overall?” and rate their self-perception of sleep quality as very good, fairly good, fairly bad, or very bad. In addition, the participant will answer two questions about how pain has interfered with sleep, classifying it in a dichotomous scale (yes or no) if "Are you awake in the middle of the night or early in the morning because of your pain?" and "Have you had trouble falling asleep because of your pain?”.

Data collection will be performed by using a standard questionnaire. The completion of all questionnaires will be supervised by an examiner for clarification in case of uncertainties and will last approximately 30 minutes per participant. The schedule will be performed as presented in Fig 1.

